### Study design

2.1

This pilot, randomized, double-blinded, sham-controlled trial is being conducted in Singapore since September 2024 (with the first patient enrolled). The study design strictly adheres to the principles of Declaration of Helsinki, Good Clinical Practice (GCP) guidelines, and mirrors STandards for Reporting Interventions in Clinical Trials of Acupuncture (STRICTA) guideline and the Consolidated Standards of Reporting Trials (CONSORT) statement, including the CONSORT-Outcomes 2022 extension (21, 22). The study lasts for a total of 14 weeks. All eligible patients first undergo a 2-week screening period, which includes providing blood samples for routine testing prior to enrollment. After the screening period, eligible patients are randomized in a 1:1 ratio to receive either EA or sham acupuncture over a 6-week intervention period, followed by a 6-week follow-up phase (Figure 1; Table 1). Sham acupuncture is selected as to offset the placebo effect of acupuncture, and there is no standard medication in treating IBS-C.

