### Outcomes and data collection

2.4

Daily symptoms recorded in physical or online patient diary include the number of BMs, SBMs, CSBMs, along with the severity of abdominal pain, discomfort, straining, and bloating, assessed using an 11-point scale (0 = none, 10 = worst possible). For each BM, stool consistency (7-point Bristol Stool Form Scale), sensation of severe straining during defecation, and use of medication are also recorded. Data will be entered electronically and stored in an encoded database within 24 h of receipt, with double data entry and range checks. Access to the trial dataset is restricted to investigators.

The primary outcome of the study is defined as responders who have a decrease in the weekly average of worst abdominal pain scores of ≥30% compared with baseline and a weekly increase of ≥1 CSBM from baseline (24). To assess the response over time, data between 2 groups will be summarized and compared throughout the treatment period and at the end of follow-up.

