### Sample size calculation

2.5

Our study is the first sham-controlled acupuncture trial that uses the Food and Drug Administration (FDA) recommended end point for IBS-C. The sample size was determined based on the study’s objectives, statistical precision, feasibility, and previously reported clinical response rates in IBS-C acupuncture trials. We referenced a randomized controlled trial by Pei et al. (28), which reported a significant difference in clinical effective rates between the acupuncture and control group. Assuming a two-sided alpha of 0.05, power of 80%, an expected response rate of approximately 70% in the acupuncture group versus 30% in the sham control group, and accounting for a 20% dropout rate and potential missing data, a total sample size of 60 patients (30 in the experimental arm and 30 in the control arm) was designed to detect clinically meaningful differences.

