### Statistical analyses

2.9

All efficacy and safety analyses will be conducted based on intention-to-treat (ITT) principle. Missing values will be imputed by the last-observation-carried-forward method. Statistical analysis will be performed using the Stata software, with statistical significance defined as a two-sided *p*-value of <0.05. Baseline characteristics will be reported as mean (SD). Baseline differences between the groups will be evaluated using Student’s t-test for normally distributed continuous variables and the non-parametric Mann–Whitney U test for non-normally distributed variables. For categorical variables, the chi-squared test or Fisher’s exact test will be applied. Comparisons between groups will be conducted by using the unpaired t-test for normally distributed data and the Mann–Whitney test for non-normally distributed data. Within-group differences will be evaluated using the paired t-test for normally distributed data and the Wilcoxon signed-rank test for non-normally distributed data.

To minimize the risk of false positives, multiple-testing correction methods will be applied during the data analysis process where appropriate. Additionally, advanced statistical methods, including the Logistic Generalized Linear Mixed Model (GLMM), will be applied. Potential inter-center differences in study outcomes will also be assessed.

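### Section 2.9 matches no group comparison clearly to the binary primary outcome on which the trial is sized; name one baseline-adjusted difference in response proportions as primary and label the GLMM supportive.

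*Protocol article*

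**What the plan says.** All references are to the Protocol article.

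- **Outcome (section 2.4).** The primary outcome is yes/no: "The primary outcome of the study is defined as responders who have a decrease in the weekly average of worst abdominal pain scores of ≥30" per cent, together with a gain of at least one CSBM per week. Groups are to be compared over the treatment period and at the end of follow-up.
- **Sizing (section 2.5).** The planned contrast is "an expected response rate of approximately 70% in the acupuncture group versus 30% in the sham control group". The test is two-sided at 0.05 with 80% power. One fifth of patients are allowed for as dropouts or missing data, and the result is 60 patients, 30 in each arm.
- **Analysis (section 2.9).** The methods come in this order:
  1. t-test or Mann–Whitney for baseline differences.
  2. "For categorical variables, the chi-squared test" or Fisher's exact test. The sentence has no qualifier of its own and follows directly on the baseline sentence.
  3. Unpaired t-test or Mann–Whitney for comparisons between groups. No test for a binary variable is named here.
  4. Paired tests for within-group change.
  5. After a sentence on multiple testing, "advanced statistical methods, including the Logistic Generalized Linear Mixed Model (GLMM), will be applied". It is introduced as an addition, with no outcome, random effect or status. The next sentence concerns differences between centres.

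**The concern.** Section 2.9 spends a paragraph naming tests, but the ones it assigns to the group comparison do not fit a yes/no responder. The tests that do fit are placed with the baseline comparisons, as a pair with no rule for choosing. A logistic mixed model is then added without a stated job. None of these is tied to a difference in proportions, which is the quantity used for sizing.

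Three things are at stake. First, the verdict on the primary outcome could depend on which of several permissible p-values is quoted. Second, if the GLMM is fitted to repeated responses, its odds ratio is on a different scale from 70% vs 30%, and those planning the larger trials mentioned in the Discussion could misread it. Third, no named group test uses baseline pain or baseline CSBM count, although both are collected and both define response.

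**Working it through.** **Inputs from the article.** Response rates 0.70 and 0.30, two-sided alpha 0.05, power 80%, dropout 20%, 30 per arm (section 2.5); 1:1 allocation (section 2.1).

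**Inputs assumed.** A less favourable true contrast of 60% vs 30%; the latent within-patient correlation; the correlation of the baselines with response. The article gives none of these.

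**1. The planned sample size reproduces.** Two proportions, pooled variance under the null, no continuity correction:

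n = [1.96·√(2·0.5·0.5) + 0.8416·√(0.7·0.3 + 0.3·0.7)]² / 0.40² = (1.386 + 0.545)² / 0.16 = 23.3, so 24 per arm.

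24 / 0.80 = 30 per arm, 60 in total, as stated. The sizing therefore corresponds to an uncorrected chi-squared comparison of two proportions.

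**2. Chi-squared against Fisher.** All 2×2 tables were enumerated with binomial weights, and p<0.05 was tested both ways.

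| True rates | n per arm | Chi-squared power | Fisher power | Opposite verdicts |
|---|---|---|---|---|
| 70% vs 30% | 30 | 89.6% | 83.8% | 5.8% |
| 60% vs 30% | 30 | 66.3% | 56.1% | 10.2% |
| 70% vs 30% | 24 | 83.6% | 75.0% | 8.6% |

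Every discordant table goes the same way: chi-squared significant, Fisher not. For example, with 17/30 vs 9/30, chi-squared = 60·(17·21 − 13·9)² / (30·30·26·34) = 4.34, p = 0.037; Fisher gives p = 0.067.

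**3. Scale of a GLMM odds ratio.** The planned marginal odds ratio is (0.7/0.3)/(0.3/0.7) = 5.44. Suppose the GLMM were fitted to repeated weekly responses with a patient random intercept. For latent correlation ρ the intercept SD is √[ρ/(1−ρ)·π²/3]. Solve E[expit(η + SD·Z)] = 0.70 for η. By symmetry the conditional odds ratio that keeps the marginal rates at 70% and 30% is exp(2η).

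| Assumed ρ | SD | Conditional OR | Ratio to 5.44 |
|---|---|---|---|
| 0.05 | 0.42 | 5.8 | 1.07 |
| 0.3 | 1.19 | 8.6 | 1.59 |
| 0.5 | 1.81 | 13.7 | 2.52 |
| 0.7 | 2.77 | 31.1 | 5.71 |

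If the random effect is for centre, with an assumed SD of 0.25 to 0.5, the ratio is 1.02 to 1.10.

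**4. What baseline adjustment offers.** Simulation with 30 per arm, 60% vs 30%, and the two baselines together correlated with latent response:

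- Correlation 0 to 0.2: about no change in power, and no loss when the baselines are uninformative.
- Correlation 0.5: from 65.5% (chi-squared) to 72.0% for the standardised difference, with null rejection of 4.5% and 4.7%. A likelihood-ratio test of the arm term reached about 74%. It rejected slightly too often when the arms did not differ, so the standardised figure is the safer one.

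**The case against.** The strongest reply is that the article condenses a fuller protocol, and that model specification and the ranking of methods are commonly left to that protocol or the SAP. That stands for missing detail: the absence of a GLMM specification is not itself a fault. It does not cover what section 2.9 does state, which is a list of between-group tests that leaves out the type of variable used for the primary outcome.

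Other parts of the reply also stand:

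- The chi-squared/Fisher sentence is not limited to baseline in its wording, responder status is categorical, and the sample size matches a chi-squared test. The authors may have meant it to cover responders.
- Fisher's lower power is its known conservatism. At 70% vs 30% with 30 per arm each expected cell is 30·0.5 = 15, so the usual small-cell convention would select chi-squared. The article does not state that convention.
- The 75% power for Fisher needs 24 analysed per arm. Section 2.9 specifies ITT with imputation, which points to 30 per arm and 83.8%, above the planned 80%.
- An unadjusted comparison of proportions would be valid. Eligibility narrows both baselines (pain of at least 3, fewer than 3 CSBMs per week), so a correlation of 0.5 may be optimistic.

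Two stronger readings are tempting and are not supported. A reader might infer that the GLMM is the only method tied to a yes/no efficacy result. The text ties it to no outcome and presents it as an addition. A reader might also infer that its odds ratio would be 2 to 6 times the planned one. That needs repeated responses, a patient random intercept and a latent correlation of about 0.41 to 0.71, none of which the article gives.

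**Conclusion.** The point holds as a mismatch in section 2.9: no named method is clearly paired with the binary responder, the two tests that would fit come without a rule for choosing, and the GLMM has no stated outcome or role. The measurable consequence is modest. Chi-squared and Fisher disagree in 5.8% of trials at the planned rates and in 10.2% at the assumed 60% vs 30%, with 30 per arm.

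The GLMM scale issue is conditional. The ratio of its odds ratio to 5.44 runs from about 1.1 to 5.7 over assumed correlations of 0.05 to 0.7, and only with a patient random intercept on repeated data. It is the same 70% vs 30% effect on another scale, so it does not show that 60 patients are too few or that the sizing is wrong.

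The case for baseline adjustment rests mainly on having one prespecified analysis on the sizing scale from data already collected. The power gain is secondary: about none at a correlation of 0 to 0.2 and several points at 0.5, all assumed.

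**What to change.** In section 2.9 and the analysis plan:

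1. Name one primary analysis: logistic regression of patient-level responder status (one yes/no value per patient, under whatever responder rule is fixed) on arm, baseline worst abdominal pain and baseline CSBM count. Standardise it over all randomised patients to give the EA-minus-sham difference in response proportions, with a 95% CI and one p-value. Take that p-value from the standardised difference.
2. Say that chi-squared and Fisher are for baseline or other categorical variables, and quote no second test for the primary outcome.
3. Label the GLMM supportive and state its outcome and random effects. If it is fitted to repeated weekly data, report standardised proportions per arm beside its odds ratio.

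The sample size stays at 60. The cost is wording, slight extra analysis work, and an effect reported on a plainer and less striking scale than an odds ratio. The change should be made before unblinding.

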### Ethics and dissemination

2.10

The trial is designed and conducted in accordance with the ethical principles outlined in the Declaration of Helsinki and the GCP guidelines. The protocol, informed consent forms, recruitment materials, and all participant materials have received approval from the NTU IRB (IRB-2023-451). Approval of both the protocol and the consent form have been obtained before any participant is enrolled. Any amendment to the protocol will require review and approval by the IRB before the changes are implemented.

### Dissemination of findings

2.11

The entire study is estimated to be completed within 3 years. De-identified results will be published in peer-reviewed scientific journals and reports to organizations, including the NTU IRB. Study findings will also be shared through social media and academic events.

### Patient and public involvement

2.12

Patients or members of the public were not directly involved in setting the research question, designing the study, selecting outcome measures, or contributing to recruitment. Patients will be informed about the study results upon completion.

## Discussion

3

This randomized, double-blinded, sham-controlled pilot trial is designed to rigorously evaluate the efficacy and safety of EA in the management of IBS-C. To our knowledge, this is the first sham-controlled acupuncture study for IBS-C. Additionally, it is the first acupuncture trial to adopt the FDA-recommended primary endpoint for IBS-C. By incorporating a biological sampling strategy to explore mechanistic insights, our comprehensive approach enables assessment not only of clinical outcomes but also of how EA may modulate gut microbiota and neurotransmitter-related metabolites associated with the brain-gut axis.

The double-blind design ensures that neither the participants nor the accessors are aware of the treatment allocation, minimizing potential biases in outcome assessment. In addition to the use of eye masks, identical acupuncture needles are applied for both the EA and sham groups. While participants may experience different sensations from the electrical stimulation, they are informed in advance that these sensations could vary from person to person. These approaches help strengthening the blinding effect between the groups.

It is important to acknowledge that the insertion of needles in the sham group may still induce minor physiological effects (29, 30). The purpose of using sham acupuncture in this study is not to compare the effects of needle insertion versus non-insertion, but to assess the difference between acupuncture at acupoints versus non-acupoints based on TCM theory. Sham acupuncture, which involves needle insertion outside these designated acupoints, serves as a necessary control measure to ensure blinding of the study. By comparing the physiological responses between the two groups, we can explore whether acupuncture at traditional acupoints provides distinct effects compared to non-acupoint areas. This approach allows us to isolate the potential impact of acupuncture grounded in traditional meridian theory, rather than just the mechanical effects of needle insertion.

Moreover, we recognize the importance of excluding patients with potential organic diseases. In addition to obtaining colonoscopy reports where available, we have implemented a comprehensive screening process. This includes blood tests, medical consultations, patient diaries, and questionnaires covering personal and family gastrointestinal history, as well as any recent unexplained weight loss. These factors are carefully considered when determining participants’ eligibility.

This study has several limitations. First, as a pilot trial with 60 participants, the findings should be interpreted with caution. Further studies with larger sample sizes are needed to confirm the results. Second, as a pilot trial conducted in Singapore, the limited geographic diversity may affect the external validity of the results. Cultural factors, diet, and genetic backgrounds could influence both the response to acupuncture and the baseline microbiota composition. Third, while sham acupuncture controls for expectation and placebo effects, there remains the possibility of physiological responses due to needle insertion. Lastly, the 6-week follow-up period may be insufficient to fully capture the long-term sustainability of EA’s effects.

In conclusion, this trial is expected to generate high-quality evidence on the clinical efficacy and potential mechanisms of electro-acupuncture for IBS-C. The findings could support EA as a non-pharmacological treatment option, inform future large-scale trials, and provide new insights into the gut-brain-microbiota interface in functional gastrointestinal disorders.

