**Figure 2 fig2:**
[figure not shown]
Anatomical locations of acupuncture and sham points.

For the EA group, disposable acupuncture needles (0.30 mm in diameter and 25–40 mm in length) are inserted obliquely at a depth of 10–30 mm into scalp acupuncture points (Baihui, Toulinqi) or straightly into body acupuncture points (Taichong, Zhangmen, Sanyinjiao, Zhongwan, Guanyuan, Tianshu, Zusanli). EA is applied to the abdominal points using fast and dispersed waves through an electric needle stimulator (ES-160 6-channel electro-acupuncture device) for 30 min. The waveform frequency is set to 5 Hz, and the current intensity is adjusted based on the patient’s comfort level, with licensed TCM practitioners continuously monitoring and adjusting the intensity during treatment to ensure safety and efficacy. The alternating stimulation is believed to produce maximal biochemical responses in the brain (26).

For the sham acupuncture group, disposable acupuncture needles (0.30 mm in diameter and 25–40 mm in length) are inserted to the similar depth as in the EA group, but at sham acupuncture points (Sham-Baihui, Sham-Toulinqi, Sham-Taichong, Sham-Zhangmen, Sham-Sanyinjiao, Sham-Zhongwan, Sham-Guanyuan, Sham-Tianshu, Sham-Zusanli; Table 2, Figure 2). The sham acupuncture points are located 1 cun away from the actual acupuncture points. For acupuncture points along the midline, the sham acupuncture points are positioned 1 cun to the left of the actual acupuncture points (based on the patient’s perspective). The sham points are not acupuncture points nor located on meridians (27). Both the EA and sham acupuncture groups follow the same procedures, including connection to the stimulator device for the same duration. In the sham group, although no electrical current is delivered, the power switch is turned on and the knobs are manipulated to produce audible clicking sounds, mimicking auditory cues of active treatment.

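### The Discussion says the sham comparison isolates acupoint location and meridian theory, but the arms also differ in electrical current, so the part due to location cannot be identified

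*Protocol article*

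**What the plan says.** The Discussion (Section 3) gives the purpose of the sham arm. It is not meant to compare needle insertion with no insertion, but "to assess the difference between acupuncture at acupoints versus non-acupoints based on TCM theory". The same paragraph says that comparing physiological responses between the groups lets the authors explore whether traditional acupoints act differently from other areas. It ends: "This approach allows us to isolate the potential impact of acupuncture grounded in traditional meridian theory", as opposed to the mechanical effect of needling alone.

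Section 2.3 (Intervention and control) describes what each arm receives.

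- **EA arm:** needles at the acupoints, and "EA is applied to the abdominal points using fast and dispersed waves through an electric needle stimulator" for 30 minutes. On the settings: "The waveform frequency is set to 5 Hz, and the current intensity is adjusted based on the patient’s comfort level".
- **Sham arm:** needles "inserted to the similar depth as in the EA group", at other sites: "The sham acupuncture points are located 1 cun away from the actual acupuncture points". The needles are connected to the stimulator for the same time, but "although no electrical current is delivered, the power switch is turned on and the knobs are manipulated to produce audible clicking sounds".

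Section 2.1 confirms that there are two arms, allocated 1:1. The Discussion mentions the electrical stimulation only as a possible difference in sensation that bears on blinding. Its limitations paragraph mentions physiological responses to needle insertion but not the current.

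**The concern.** The Discussion presents needle location as the factor under test. In the design, location and current change together, and no arm receives one without the other. The article does not treat the current as inert: Section 2.3 credits the alternating stimulation with a strong biochemical effect in the brain.

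What is at stake is attribution. A reader who relies on the Discussion would take a positive result as evidence that acupoints work better than neighbouring sites, and so as support for meridian theory. The same result could come entirely from the current, or from current and location acting together.

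**Working it through.** **Step 1. What differs between the arms (Section 2.3)**

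| Factor | EA | Sham | Differs? |
|---|---|---|---|
| Needle location | acupoints | 1 cun away | yes |
| Electrical current | 5 Hz, abdominal points, 30 min | none | yes |
| Insertion depth | as specified | similar | not by plan |
| Connection to stimulator, duration | yes | yes, same duration | no |

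Two factors differ. A layout crossing location with current has four cells, and this trial fills two of them. The cells for acupoints without current and non-acupoints with current are empty.

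**Step 2. What the contrast estimates**

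Let m(L, C) be the mean outcome, with L = 1 for acupoints and C = 1 for current. EA is m(1,1) and sham is m(0,0). Then

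m(1,1) − m(0,0) = [m(1,0) − m(0,0)] + [m(0,1) − m(0,0)] + [m(1,1) − m(1,0) − m(0,1) + m(0,0)]

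That is, the difference equals the location effect plus the current effect plus their interaction. There is one estimable quantity and three unknowns. In any regression on these arms, including the logistic mixed model named in Section 2.9, the indicators for location and current are the same column. More patients or a different model cannot separate them.

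Current goes only to the abdominal points, so scalp and limb points differ between arms by location alone. This does not help, because outcomes are measured per patient and not per point.

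**Step 3. The plan's own figure**

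Inputs from Section 2.5: 70% versus 30%, two-sided alpha 0.05, power 80%, dropout 20%.

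- With pooled variance under the null and no continuity correction, n = [1.960 × √(2 × 0.5 × 0.5) + 0.842 × √(0.7 × 0.3 + 0.3 × 0.7)]² / 0.40² ≈ 23.3, so 24 per arm.
- Dropout: 24 / (1 − 0.20) = 30 per arm, 60 in total.

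The stated 60 is reproduced. The calculation concerns the difference between the two arms as delivered, and nothing in it depends on a location-only reading.

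**Step 4. How wide the ambiguity is**

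Suppose 70% versus 30% were observed. Assume that moving to acupoints without current does no harm, and that adding current at acupoints does no harm. Then 30% ≤ m(1,0) ≤ 70%.

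| Share of the 40 points due to location | Implied response, acupoints without current |
|---|---|
| none | 30% |
| a quarter | 40% |
| half | 50% |
| three quarters | 60% |
| all | 70% |

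Every row gives the same two arms, so the trial data would fit each equally well.

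**Step 5. A null result**

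Without the no-harm assumption, opposing effects of location and current could cancel. A difference near zero would therefore not show that location is irrelevant.

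**The case against.** The strongest reply is that the trial does not set out to test location. The Introduction aims to evaluate EA and hypothesises that EA is superior to sham. Section 2.1 randomises to EA or sham, and the conclusion of the article speaks of EA. All of these refer to the package, which the design does compare. This stands: the objective needs no rewording, and no stated hypothesis or test depends on a location-only contrast.

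A second reply is that the claim in the Discussion is hedged. It speaks of a potential impact and sets it against the mechanical effect of needling, for which similar-depth sham insertion does control. Section 2.3 also discloses openly that "although no electrical current is delivered, the power switch is turned on and the knobs are manipulated to produce audible clicking sounds". This softens the claim but does not rescue it. Controlling for insertion does not control for current, and a stated purpose of "to assess the difference between acupuncture at acupoints versus non-acupoints based on TCM theory" still goes beyond the design.

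A reader might also infer more than the documents support:

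- **That none of an observed difference is due to location.** Confounding leaves the share unknown; it does not make it zero. Under the assumption in the working, location could account for none or all of it.
- **That the microbiota and metabolite aims fail too.** The Introduction, Section 2.8 and the opening of the Discussion attribute those changes to EA, which includes the current. They do not require the two factors to be separated. The affected sentence is the one in the Discussion that contrasts physiological responses at acupoints and elsewhere.
- **That the trial is invalid.** Randomisation, endpoint, sample size and analysis do not rest on the isolation claim.

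**Conclusion.** The point holds and is confined to the attribution made in the Discussion. That text gives the comparison a property it lacks: Section 2.3 makes location and current differ together, so the location share of any between-arm difference is not identifiable, and a null result would not isolate location either. At the planning rates, the response to acupoint needling without current is bounded only between 30% and 70%, and even that range assumes that neither step is harmful. The non-identifiability itself needs no assumption beyond the two arms as described.

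The comparison of EA as a package against sham remains valid, as do mechanistic claims about EA as a whole. The text should be corrected, preferably before unblinding, but the fault does not threaten the validity of the trial.

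**What to change.** 1. In the Discussion, describe the contrast as acupoint needling plus electrical current versus non-acupoint needling without current.
2. Remove the sentences that claim to isolate acupoint location or meridian theory, including the one that infers acupoint-specific effects from physiological responses in the two groups.
3. Add to the limitations paragraph that location and current are confounded and that their separate contributions cannot be estimated.

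The objective in the Introduction, the sample size in Section 2.5 and the analysis in Section 2.9 can stay as they are. The cost is a few sentences and a narrower claim: a positive result would support the EA package over this sham, without saying which component was responsible.
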